### 2.5 Study population

At the first consultation, a form containing the patient's medical history will also be completed. Subsequently, these volunteers will undergo a clinical examination to determine their oral conditions. Based on the information collected in this first visit, the study will follow the Inclusion and Exclusion criteria.

#### 2.5.1 Inclusion criteria

Children aged 3 to 6 years, with at least one anterior deciduous tooth with irreversible pulpitis or pulp necrosis due to caries or trauma, with at least 2/3 of root remaining, and children who have not undergone antibiotic therapy within three months previous.

### 2.5.2 Exclusion criteria

Children with compromised health, with deciduous teeth with 2/3 or more root resorption, and crypt involvement.

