The technique called Lesion sterilization and tissue repair therapy (LSTR) was proposed for non-vital deciduous teeth, with advanced root resorption, strategically important teeth, with bone loss, mobility, radiolucency in the furcation area, uncooperative patients who cannot undergo extraction at that time. This technique, however, is contraindicated for patients allergic to any of the components of the antibiotic agents used, extensive internal or external resorption, teeth close to exfoliation, perforation of the pulp floor and children with bacterial endocarditis. The combination

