of drugs is used to minimize the amount of microorganisms present in the lesion or in the root canal and tissue repair is expected if the lesion is disinfected. When applied to treat necrotic pulps in deciduous teeth, it is performed without instrumenting the root canals, that is, without conventional chemical-mechanical preparation and an association of antimicrobials is deposited in the entrances of the root canals. The LSTR approach or non-instrumental endodontic treatment (NIET) therefore involves the use of an association of antimicrobial drugs and has advantages such as less time, less complexity, prevention of irritation of the periapical tissues and the germ of the permanent successor, in addition to being able to be used in deciduous teeth that present a rhizolysis process of up to more than a third of the roots. without the conventional chemical-mechanical preparation and an association of antimicrobials is deposited in the entrances of the root canals. The LSTR approach or non-instrumental endodontic treatment (NIET) therefore involves the use of an association of antimicrobial drugs and has advantages such as less time, less complexity, prevention of irritation of the periapical tissues and the germ of the permanent successor, in addition to being able to be used in deciduous teeth that present a rhizolysis process of up to more than a third of the roots. without the conventional chemical-mechanical preparation and an association of antimicrobials is deposited in the entrances of the root canals. The LSTR approach or non-instrumental endodontic treatment (NIET) therefore involves the use of an association of antimicrobial drugs and has advantages such as less time, less complexity, prevention of irritation of the periapical tissues and the germ of the permanent successor, in addition to being able to be used in deciduous teeth that present a rhizolysis process of up to more than a third of the roots.

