The filling materials for deciduous teeth must have the following properties: resorbable, radiopaque, bactericidal, promote adequate filling and adherence to the walls of the root canals, easily removed when necessary; in addition to not causing damage to the periapical tissues and to the permanent tooth germ, nor altering the color of dental structures. However, there is no single material that fulfills all the desirable requirements for a filling material, in addition to there being no consensus in the literature about the best material to be used in the endodontics of deciduous teeth.

Among the filling materials for deciduous teeth, we have the Guedes Pinto paste and the CTZ antibiotic paste. The Guedes-Pinto paste is composed of iodoform, camphorated paramonochlorophenol and an association of corticoid and antibiotic (Rifocort) and has been widely used due to its antimicrobial and antiseptic properties, in addition to being

radiopaque and resorbable, thus, it does not harm the process of rhizolysis of the deciduous tooth and the eruption of the permanent successor. The CTZ antibiotic paste, on the other hand, is composed of chloramphenicol, tetracycline and eugenol zinc oxide has been especially indicated in public health services and in cases of patients who are not cooperative. It presents easy manipulation, biological compatibility; however, there are still controversies regarding the safety of using chloramphenicol. 

The success of endodontic treatment is directly related to intracanal bacterial decontamination and there is a difficulty in endodontic treatment in deciduous teeth, often due to difficult child control, internal anatomy of root canals, and root resorption. Considering these factors, it becomes necessary to know the effectiveness of non-instrumented endodontic treatment (NIET) in deciduous teeth associated with the use of two filling pastes. Therefore, carrying out this clinical study to evaluate the effectiveness of non-instrumental endodontic treatment in deciduous teeth, comparing the performance of CTZ paste and Guedes-Pinto paste, will support the analysis for choosing the most appropriate protocol.

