### 2.3 Ethical aspects

The study will be conducted ethically according to the criteria described in the Declaration of Helsinki (World Medical Association Declaration of Helsinki, 2008). The protocol for this study will be submitted for approval by the Research Ethics Committee of the Metropolitan University of Santos (UNIMES). All information will be present in the free and informed consent form (Resolution no. 196 of the National Health Council, Ministry of Health, Federal District, Brazil, 03/10/1996), which will be signed in two copies, one belonging to the responsible, and another to the researchers.

Study participants will also be instructed that they may withdraw from the study at any time, for any reason, if they so choose. Researchers will also be able to remove participants from the study if they deem it necessary.

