### 2.4 Determination of sample size

To carry out the sample calculation, a 12-month success rate for the CTZ paste of 86.4% was assumed. The non-inferiority limit was considered as 15%, power of 80% and significance level of 5%, which resulted in 38 teeth per group. 20% were added to this number due to possible sample losses and 40% due to the patient having more than one tooth included, resulting in a sample of 60 deciduous anterior teeth per group, totaling 120 deciduous anterior teeth.

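### The entry criteria do not exclude a child with a known allergy to a paste antibiotic, although the protocol's introduction calls the technique contraindicated in such a child

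*Protocol*

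**What the plan says.** Section 1 (Introduction) lists situations in which lesion sterilization and tissue repair should not be used. One is allergy: the technique is "contraindicated for patients allergic to any of the components of the antibiotic agents used". The same section then treats that technique and the trial's own as one: "The LSTR approach or non-instrumental endodontic treatment (NIET) therefore involves the use of an association of antimicrobial drugs".

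Section 2.6 gives this treatment to both groups, each with its own paste. CTZ contains chloramphenicol and tetracycline (section 2.8.1). Guedes-Pinto paste contains "an association of corticoid and antibiotic (Rifocort", as the introduction puts it, and section 2.8.2 confirms the product in the mixing instructions.

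The only antibiotic-related entry rule is in section 2.5.1, which admits "children who have not undergone antibiotic therapy within three months previous". Section 2.5.2 excludes "Children with compromised health, with deciduous teeth with 2/3 or more root resorption, and crypt involvement". Section 2.5 has a medical-history form completed at the first consultation, and adds: "Based on the information collected in this first visit, the study will follow the Inclusion and Exclusion criteria". Section 2.7 assigns the treatment by a draw for each tooth.

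**The concern.** The protocol states a contraindication to the technique that every participant will receive, and then leaves it out of the rules that decide who may receive it. Participants are 3 to 6 years old. Followed to the letter, the criteria admit a child for whom the protocol's own background says the technique should not be used.

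Randomization makes the omission matter more than it would in ordinary care. A clinician free to choose could pick the paste without the offending drug. Here the draw decides. If the allergy is noticed only after the draw, the choice is between exposing the child and departing from the allocation.

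What is at stake is the safety of individual children. The estimate of the treatment difference, the sample size and the trial's conclusion are not affected.

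**Working it through.** The protocol gives no figure on this point, so there is none to reproduce. The check sets its statements side by side.

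**Step 1. Does the contraindication apply to this trial?** The introduction's warning concerns lesion sterilization and tissue repair, and the introduction equates that with the non-instrumented technique. Both groups receive it. The warning refers to the antibiotic agents used, so the contents of each paste decide its reach:

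| Paste | Antibiotic content according to the protocol | Where |
|---|---|---|
| CTZ (Group 1) | chloramphenicol, tetracycline | Sections 1 and 2.8.1 |
| Guedes-Pinto (Group 2) | Rifocort, a corticoid with an antibiotic | Sections 1 and 2.8.2 |

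Pastes containing an antibiotic: 2 of 2. The warning applies to both arms.

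**Step 2. Do the entry criteria carry it over?**

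| Condition | Section | Names allergy? |
|---|---|---|
| Age 3 to 6 years | 2.5.1 | No |
| Anterior primary tooth with irreversible pulpitis or necrosis | 2.5.1 | No |
| At least 2/3 of the root remaining | 2.5.1 | No |
| No antibiotic treatment in the last three months | 2.5.1 | No (recent use only) |
| Compromised health | 2.5.2 | No (undefined) |
| Root resorption of 2/3 or more | 2.5.2 | No |
| Crypt involvement | 2.5.2 | No |

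Conditions: 4 + 3 = 7. Conditions naming allergy: 0. A child with a known allergy can easily meet the three-month rule, since it asks about use and not about reaction.

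Other contraindications from the same sentence of the introduction fare better. Extensive resorption has a direct counterpart in 2.5.2, and bacterial endocarditis would plausibly count as compromised health. Allergy has no clear counterpart.

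**Step 3. Does another provision catch such a child?**

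- *Medical-history form (2.5).* It may bring an allergy to light, but eligibility then follows the listed criteria, and those give no rule for acting on the answer.
- *Compromised health (2.5.2).* The term is not defined. An otherwise healthy child with a drug allergy does not plainly fall under it, and two operators could decide differently.
- *Removal by the investigators (2.3).* The text is "Researchers will also be able to remove participants from the study if they deem it necessary". This is a general discretion and sets no entry rule.

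**Step 4. What happens to such a child once enrolled?** Allocation is 1:1 (section 2.2) and made per tooth (section 2.7). For a child allergic to an antibiotic in one paste only:

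chance per tooth of drawing that paste = 1/2.

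The sample-size section expects some children to contribute several teeth; it adds "40% due to the patient having more than one tooth included". For a child with two study teeth, taking the two draws as independent (an assumption):

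- chance that at least one tooth draws the paste in question = 1 − (1/2)² = 3/4;
- chance that the child receives both pastes = 2 × 1/2 × 1/2 = 1/2.

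An exclusion tied to one paste would therefore not be enough. These chances are conditional on such a child being enrolled. How often that would happen cannot be worked out from the protocol.

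**The case against.** The strongest reply is that this is silence and not a conflict. The introduction summarizes the literature and sets no rule for the trial, and nothing in section 2.5 tells anyone to treat an allergic child. The history form comes before eligibility is decided and before the draw. Compromised health is the only criterion on general health and is left open. Since endocarditis can be covered only by that phrase, it may serve as shorthand for all medical contraindications. On that reading the defect is a vague term. Beyond this stand ethics-committee review, the commitment to the Declaration of Helsinki and the power to remove a participant. For harm to occur, a clinician would have to know of the allergy and place the paste anyway. Finally, the introduction speaks only of antibiotic components, while the remedy proposed here covers every component.

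Part of this stands. The history form is not shown and may ask about allergy, so nothing can be claimed about what happens in practice. The counts in the check describe the text and do not measure risk. Extending the exclusion to eugenol, zinc oxide, iodoform and camphorated paramonochlorophenol goes beyond what the introduction requires, although it is sensible practice.

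The main point survives. A phrase that may or may not reach a drug allergy in a healthy child is not a safeguard for a hazard the protocol itself names. A history form that feeds only the listed criteria cannot supply a missing one, and discretion to remove is not a rule on entry. Nor can this be left to the statistical analysis plan, because eligibility belongs in the protocol.

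**Conclusion.** The concern holds. The entry criteria do not carry over a contraindication that the protocol's own introduction states, although the technique is given in both arms and both pastes contain an antibiotic. As written, an otherwise healthy child with a known allergy to a paste antibiotic is eligible, and the draw then takes the choice of paste out of the clinician's hands.

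Its weight is that of a safety correction that should be made. No trial-level risk is claimed, because the protocol gives no frequency of allergy. The conclusion rests on two readings of the text: that the introduction's equation of the two techniques is meant literally, and that undefined compromised health does not clearly include a drug allergy. If the investigators already read it as including allergy, writing that down settles the matter.

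**What to change.** Add one exclusion to section 2.5.2: *known allergy or hypersensitivity to any component of either paste*. State that it is checked on the medical-history form of section 2.5 before the draw in section 2.7. It must cover both pastes for every child, whichever paste is drawn first.

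The form item should list the components by name: chloramphenicol, tetracycline, zinc oxide and eugenol for CTZ; iodoform, camphorated paramonochlorophenol and Rifocort for Guedes-Pinto. The antibiotic and the corticoid in Rifocort should be spelled out, since the protocol gives only the product name.

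The cost is one line in the protocol and one item on an existing form. The only downside is that a few children may be screened out. The design, the sample size and the analysis stay as they are.

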### 2.6 Study Groups

| GROUP | INTERVENTION              |
|-------|---------------------------|
| G1    | NIET + CTZ                |
| G2    | NIET + Guedes-Pinto Paste |

### 2.7 Randomization

The type of treatment will be randomly determined for each tooth, through a draw before the intervention. The draw will follow the order electronically generated by the randomizer.org randomization website for a balanced distribution of all teeth between the groups.

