### 2.8 Interventions

#### 2.8.1 Group 1. NIET + CTZ Paste

In group 1, the following endodontic treatment protocol will be performed:

1. Initial X-ray
2. Perform the anesthetic technique and isolate the operative field;
3. Remove tissues with low or high speed burs and/or dentin spoon until exposing the pulp chamber;
4. Remove the roof of the pulp chamber with inactive tip drills and remove pulp debris. Wash the pulp chamber with saline solution;
5. Locate the root canals;
6. Perform a final saline cleaning of the coronary chamber and dry with sterile cotton balls;
7. Prepare the CTZ paste: The powder that makes up the CTZ paste will be manipulated in a 1:1:2 ratio (500mg of Chloramphenicol, 500mg of Tetracycline and 1,000mg of Zinc Oxide) by Formula & Action (F&A) and incorporated into

the liquid eugenol at the time of use, with the aid of a flexible spatula nº 24 and on a sterile glass plate.

8. Insert the CTZ paste and apply light pressure with cotton balls;
9. Protect the CTZ paste with a thin layer of gutta-percha. Place the slightly warmed gutta-percha and place it on the floor of the pulp chamber, carefully at the entrances of the root canals;
10. Clean the cavity with cotton balls and alcohol;
11. Perform the restoration;
12. Finally, perform the final radiograph

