#### 2.8.2 Group 2. NIET + Guedes-Pinto Paste

In group 2, the following endodontic treatment protocol will be performed:

1. Initial X-ray
2. Perform the anesthetic technique and isolate the operative field;
3. Remove tissues with low or high speed burs and/or dentin spoon until exposing the pulp chamber;
4. Remove the roof of the pulp chamber with inactive tip drills and remove pulp debris. Wash the pulp chamber with saline solution;
5. Locate the root canals;
6. Perform a final saline cleaning of the coronary chamber and dry with sterile cotton balls;
7. Prepare the Guedes-Pinto paste: Place 1 cm of Rifocort®, 1 cm of Iodoform and 2 drops of Camphorated Paramonochlorophenol (PMCC), incorporate the medicines with the help of a flexible spatula nº 24 and on a sterile glass plate.
8. Insert the Guedes-Pinto paste and apply light pressure with cotton balls;
9. Protect the Guedes-Pinto paste with a thin layer of gutta-percha. Place the slightly warmed gutta-percha and place it on the floor of the pulp chamber, carefully at the entrances of the root canals;
10. Clean the cavity with cotton balls and alcohol;
11. Perform the restoration;
12. Finally, perform the final radiograph

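### The paste is drawn before the intervention although the arms do not differ until step 7; opening a concealed allocation after step 6 would be a cheap improvement

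*Protocol*

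**What the plan says.** Section 2.7 fixes both the unit and the timing of randomisation: "The type of treatment will be randomly determined for each tooth, through a draw before the intervention". It continues: "The draw will follow the order electronically generated by the randomizer.org randomization website for a balanced distribution of all teeth between the groups". It does not say who makes the draw, who sees the result, or when the operator learns it.

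Section 2.8 lists twelve steps for each arm. The chamber is first reached at step 3 ("Remove tissues with low or high speed burs and/or dentin spoon until exposing the pulp chamber") and debrided at step 4 ("Remove the roof of the pulp chamber with inactive tip drills and remove pulp debris. Wash the pulp chamber with saline solution"). The last step before the paste is step 6: "Perform a final saline cleaning of the coronary chamber and dry with sterile cotton balls". At step 7 the CTZ powder is mixed with "the liquid eugenol at the time of use, with the aid of a flexible spatula nº 24 and on a sterile glass plate". The Guedes-Pinto components are also combined on a glass plate at step 7.

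The only masking described is in section 2.9, for the two readers of the radiographs. Section 2.10 names an intention-to-treat analysis.

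**The concern.** The paste is the only intended difference between the arms, and no step before step 7 needs the allocation. If the draw is made earlier and the operator sees it, two things become possible.

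- **Unequal debridement.** The canals are not instrumented, so much of the mechanical cleaning is the chamber work in steps 3 to 6. How thorough it is depends on the operator. In a non-inferiority trial (section 2.2), extra care for the paste thought weaker would shrink a true difference and favour a conclusion of non-inferiority.
- **Informed loss of teeth after randomisation.** The pulp and the chamber floor are first seen directly during these steps. The Introduction lists floor perforation and extensive internal resorption among the contraindications to the technique, and section 2.3 lets researchers remove participants at their discretion. A tooth abandoned at that point has already been randomised, and the person deciding may know its arm.

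A related point arises because randomisation is per tooth and section 2.4 expects some children to contribute more than one. If the draws are known early, they could influence which tooth is treated next.

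**Working it through.** **Side-by-side reading of sections 2.8.1 and 2.8.2**

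| Step | Group 1 and Group 2 |
|---|---|
| 1. Radiograph | same wording |
| 2. Anaesthesia and isolation | same wording |
| 3. Reaching the chamber | same wording |
| 4. Roof and debris removed, chamber washed | same wording |
| 5. Finding the canals | same wording |
| 6. Final cleaning and drying | same wording |
| 7. Paste prepared | differs: first arm-specific step |

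Six of the six steps before paste preparation are identical. Section 2.8 is headed as the interventions and numbers these steps within them, so the plain reading of 2.7 puts the draw before step 1.

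**Scale of one affected tooth**

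The protocol gives no figure on this point to reproduce. These are illustrations, not estimates of bias. Inputs: 60 teeth per group and an assumed success rate of 86.4% (section 2.4). That rate is a 12-month figure from a cited trial in primary molars, whereas this trial follows anterior teeth for 6 months, so it serves only as a reference point.

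- Expected successes: 0.864 × 60 = 51.8, taken as 52. Expected failures: 0.136 × 60 = 8.2, taken as 8. Starting rate: 52/60 = 86.7%.
- One outcome changed, tooth retained: 1/60 = 1.7 points.
- One would-be success dropped: 51/59 = 86.4%, a change of about −0.2 points.
- One would-be failure dropped: 52/59 = 88.1%, a change of about +1.5 points.
- Three outcomes changed, all in the same direction and in one arm: 3/60 = 5.0 points, one third of the 15-point limit.
- Three would-be successes dropped from one arm: 49/57 = 86.0%, a change of about −0.7 points.

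A dropped tooth leaves the denominator as well as the numerator, so dropping a tooth and changing its outcome must be kept apart. The documents give no number of affected teeth of either kind.

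**The case against.** The strongest reply is that a draw before the procedure contradicts nothing in the protocol and misstates nothing. This stands: the point is a refinement.

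The other objections reduce the point without removing it.

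- *Knowledge of the arm is inferred.* A reader might conclude that the operator does know the paste during steps 1 to 6. The protocol does not say so; it only provides no safeguard. The supportable statement is that the operator may know.
- *The timing might be meant loosely*, as just before the paste is placed. The layout of section 2.8 speaks against this. If it is what the sponsor intends, section 2.7 should say so.
- *Teeth found untreatable on opening may be rare.* The eligibility criteria in 2.5.1 and 2.5.2 contain no exclusion after opening. The Introduction and section 2.3 make the event possible, but its frequency is unknown.
- *The intention-to-treat analysis covers dropped teeth.* It does so in part. A tooth abandoned before any paste is placed has no outcome on its allocated paste, and intention to treat does nothing about uneven debridement.
- *The early draw spares a pause in a young child.* The protocol stresses difficult cooperation and short chair time, so the cost is not nil. However, both pastes are mixed at step 7 in any case.
- *Opening the allocation later hides nothing if the operator can see the generated list.* This is correct, so the fix must include concealment.

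A reader might also infer that the early draw biases the restoration (step 11, "Perform the restoration", with no type named). It does not follow. The operator has seen the paste by then whenever the draw is made, so the restoration type is a separate matter.

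**Conclusion.** The point holds as a cheap improvement. Section 2.7 fixes a draw before the intervention, steps 1 to 6 are the same in both arms, and no masking of the operator is described. There is therefore an avoidable opportunity for debridement, or the decision to abandon a tooth, to depend on the arm. No bias is shown to have occurred.

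Its size cannot be derived from the documents. It would be tempting to say that three teeth handled differently or dropped cost 5 points, a third of the non-inferiority limit. That holds only if three outcomes actually change, all in one direction and in one arm, and the count of three would be an assumption. For dropped teeth the shift per tooth is smaller.

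The conclusion rests on two assumptions: that the operator can see the draw, and that the draw precedes step 1. The benefit of a change is confined to steps 1 to 6, because the operator necessarily knows the paste from step 7 on.

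**What to change.** Replace the timing rule in section 2.7 with: *The allocation for each tooth is kept concealed from the operator and opened only after step 6, once the tooth has been confirmed treatable and entered by number; in a child with several eligible teeth, the treatment order is recorded before the first allocation is opened.*

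Teeth abandoned on opening then fall before randomisation, and the shared steps are carried out without knowledge of the arm. No paste, clinical step or sample size changes. The cost is one sentence in the protocol, a means of holding the allocation out of the operator's sight, and a short chairside pause before the paste is mixed.

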### **2.2 Experimental Design**

The present work is characterized as a controlled and randomized clinical trial of non-inferiority, with two parallel arms and allocation rate of 1:1 and which will be carried out at the Dental Clinic of the Metropolitan University of Santos (UNIMES). Because it is a randomized clinical trial and seeking greater transparency and quality of this research, we will use the CONSORT recommendations (Consolidated Standards of Reporting Trials). The study protocol was registered on the international platform of clinical trials ClinicalTrials.gov, with registration number NCT04587089

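### The paste is drawn tooth by tooth without regard to the child, so about half of two-tooth children get one paste only and part of the within-child comparison is given up by chance

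*Protocol*

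**What the plan says.** Protocol section 2.7 makes the tooth the unit of randomisation: "The type of treatment will be randomly determined for each tooth, through a draw before the intervention". The order comes from a website generator and is meant to serve "for a balanced distribution of all teeth between the groups". No blocking or stratification by child is mentioned.

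Several teeth per child are expected. Section 2.5.1 admits children "with at least one anterior deciduous tooth with irreversible pulpitis or pulp necrosis" and sets no upper limit. Section 2.4 enlarges the sample by "40% due to the patient having more than one tooth included", giving 60 teeth per group and 120 in all.

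Section 2.2 describes a "controlled and randomized clinical trial of non-inferiority, with two parallel arms and allocation rate of 1:1". Section 2.10 takes the tooth as the unit of analysis, compares the groups with Student's t or Mann-Whitney, and names no child term. A within-child comparison is planned nowhere.

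**The concern.** Teeth in one mouth share hygiene, diet, age, cooperation and healing. When a child receives both pastes, these shared factors drop out of the contrast between that child's teeth. When all of a child's teeth receive the same paste, the child informs only the noisier comparison between children.

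The protocol already lets one child receive both pastes, and it pays for multi-tooth children in sample size, but it leaves to chance whether the pastes are split within the child. What is at stake is precision against a 15-point non-inferiority limit. The validity of the randomisation is not in question.

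**Working it through.** **Inputs from the protocol.** 120 teeth, 60 per paste (2.4); one order balanced over all teeth (2.7); success 86.4%, limit 15 points, power 80%, significance 5% with sidedness not stated (2.4).

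**Assumptions not in the protocol.** Intra-child correlation r from 0.1 to 0.5; number of teeth per child; a random order of 60 and 60. A list in small blocks would change the chance of a shared paste, but 2.7 states none.

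**1. The plan's own figures.** The inflation step reproduces: 38 × (1 + 0.20 + 0.40) = 60.8, against the stated 60. The 38 itself does not follow from the stated inputs. With equal success at 86.4%, (1.645 + 0.842)² × 2 × 0.864 × 0.136 / 0.15² gives 65 per group at one-sided 5%, and 82 at one-sided 2.5%. That is a separate matter and does not decide this one.

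**2. Chance that all teeth of one child get the same paste**, 2·C(60,m)/C(120,m):

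- m = 2: 59/119 = 49.6%
- m = 3: (59/119) × (58/118) = 24.4%
- m = 4: 24.4% × (57/117) = 11.9%

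So about half of two-tooth children, 76% of three-tooth and 88% of four-tooth children receive both pastes anyway.

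**3. Information on the paste difference, all teeth in pairs** (60 pairs, unit variance, generalised least squares with exchangeable correlation):

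- Per-tooth draw, about 30 split and 30 same-paste pairs: 15/(1−r) + 15/(1+r) = 30/(1−r²)
- Every pair split: 30/(1−r)
- Ratio: 1 + r, that is 1.10, 1.20, 1.30 and 1.50 at r = 0.1, 0.2, 0.3 and 0.5

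**4. Half the teeth in pairs** (60 one-tooth children and 30 pairs). Single teeth contribute 15 under either draw.

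| r | Per-tooth draw: 15 + 15/(1−r²) | Split: 15 + 15/(1−r) | Ratio |
|---|---|---|---|
| 0.1 | 30.15 | 31.67 | 1.05 |
| 0.2 | 30.63 | 33.75 | 1.10 |
| 0.3 | 31.48 | 36.43 | 1.16 |
| 0.5 | 35.00 | 45.00 | 1.29 |

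The standard error falls by 1 − 1/√ratio: 2.4% at a ratio of 1.05 and 18.4% at 1.50.

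**5. Power.** Take equal success at 86.4%, one-sided 5%, all teeth in pairs and the child modelled. With 60 teeth per group the standard error for independent teeth is √(2 × 0.864 × 0.136/60) = 0.0626, and power is about 77%. The variance factor is 1−r² for the per-tooth draw and 1−r for the split.

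| r | Teeth per group | Per-tooth draw | Split |
|---|---|---|---|
| 0.1 | 60 | 78% | 81% |
| 0.3 | 60 | 81% | 89% |
| 0.3 | 48 (20% lost, pairs intact) | 73% | 82% |

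**6. Type of child effect.** With a fixed child effect, one-tooth children contribute nothing to the paste contrast. In the setting of step 4 the split design then carries only 15/(1−r) = 18.8, 21.4 and 30.0 at r = 0.2, 0.3 and 0.5. That is below the 30.6, 31.5 and 35.0 of the present draw with a random child effect.

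**The case against.** Nothing here is stated wrongly. Section 2.2 promises two parallel arms at 1:1, and a tooth-level draw delivers that without bias. A reader might infer that the randomisation is flawed or that the within-child comparison is lost. The protocol supports neither: the draw is valid, and step 2 shows that many multi-tooth children receive both pastes by chance. This objection stands and limits the point to efficiency.

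The size of the gain rests on assumed quantities. At r = 0.1 with half the teeth in pairs it is 5% more information, and with fewer multi-tooth children it is smaller still. This also stands.

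Changing 2.7 alone would not deliver the gain. The tests named in 2.10 ignore the child, so the reported standard error would not shrink. The analysis has to change too, and in the right form (step 6).

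Splitting has a cost. All teeth are anterior, and the primary outcome in 2.9 includes spontaneous pain and gingival edema, which may be hard to assign to one of two neighbouring teeth. Misassignment would tend to pull the arms together, which is the wrong direction in a non-inferiority trial. However, the present draw already gives both pastes to about half of two-tooth children, so splitting makes an existing difficulty more frequent and does not create it.

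**Conclusion.** The point holds as an inexpensive improvement in efficiency. The protocol expects several teeth per child and draws their pastes without regard to the child, so 49.6% of two-tooth children, 24% of three-tooth and 12% of four-tooth children would contribute no within-child contrast. For r between 0.1 and 0.5, splitting adds about 10–50% information if all teeth come in pairs and about 5–29% if half do. These figures assume exchangeable correlation and an analysis that models the child.

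A reader might go further and conclude that the per-tooth draw leaves the trial short of its power target. The protocol does not allow that conclusion, because it gives neither the correlation nor the number of teeth per child. Under the assumptions of step 5 at r = 0.3, the present draw with the child modelled reaches 81% before losses. After 20% losses it gives 73%, against 82% for the split, so the allocation could matter to the target without being shown to decide it.

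**What to change.** **Section 2.7.** List all eligible teeth of a child first, then draw their pastes in one step, balanced within the child: two teeth get one paste each in random order, four get two each. Draw single teeth, the odd tooth of three, and any tooth that becomes eligible later from a separate balanced list. Drawing together matters because the last tooth's paste could otherwise be predicted from the others.

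**Section 2.10, or the SAP if the model is set there.** Compare the pastes with a model that has a random child effect, or GEE with exchangeable correlation. Do not use a fixed child block, so that one-tooth children still contribute.

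**Section 2.9.** State how pain and edema are assigned to a tooth when neighbouring teeth carry different pastes.

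**Cost.** A new list and short changes to these sections, with no extra teeth or visits. The price is the more frequent assignment problem. If few multi-tooth children are expected the gain is small, so the sponsor should state the expected number of teeth per child.
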